| Mood Check        |                           | Writing Manipulation Check                                       | Writing Manipulation Check                                                                                  |   | x |   |   |
| Covariates        |                           | Demographic information                                          | Race/ethnicity, age, education, income, occupation                                                          | x |   |   |   |
|                   |                           | Clinical information                                             | Age at diagnosis, time at diagnosis, cancer stage, treatment                                                | x |   |   |   |
|                   |                           | Clinical update                                                  | Cancer recurrence                                                                                           | x |   | x | x |

baseline and 6- and 12-month follow-ups. Clinical information will also be obtained through medical records with patients' consent, a procedure successfully used in pilot studies.

Moderating variables and demographics will be self-reported at baseline. Potential psychosocial mediators will be self-reported at baseline and at the 6-week and 6-month follow-ups. The three assessments of mediators will allow for inference of mechanisms in longitudinal models. We will assess biomarkers at baseline and 6-week follow-up, based on the literature. We will also assess self-reported perceived stress at the 6-week follow-up so that objective and subjective measures of stress are expected to be collected at the same time. The Global Mood and Life Satisfaction Sliders will be used at baseline and after each writing session to measure mood. Writing Manipulation Check will be used after completing three writing sessions.

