- Biomarkers. Following the recommended procedure of assessing stress biomarkers in RCTs, stress-related biomarkers (salivary cortisol and alpha-amylase) will be assessed via saliva samples collected four times per day over two consecutive days before and after the intervention. Salivary cortisol and alpha-amylase levels will be assessed at study entry and at the 6-week follow-up four times a day, starting 20 minutes after waking up in the morning, 1200, 1700, and 2100 hours on each of two consecutive days. Following established procedures, patients will be given detailed instructions on collecting their own saliva on their own. Patients will be asked to refrain from eating, chewing gum, exercising, smoking, brushing teeth, and drinking anything except water *for 1 hour before sampling*; and to complete questions (see Appendix A) regarding comorbid conditions (e.g., autoimmune disorders) and medications that may influence cortisol or alpha-amylase levels (e.g., prednisone, dexamethasone, and other steroids) during the sampling period. They will be given a medical bottle equipped with a Medication Event Monitoring Systems Cap (AARDEX Group, Belgium^65), an electronic device that has been shown to reliably track the time a saliva sample is taken. Patients will be asked to mail their samples to our laboratory soon after collection. Retuning the sample within 5 days is a general guideline based on the feasibility and sample quality. However, it is acceptable for the participants to mail the saliva samples within 2 - 4 weeks, because salivary cortisol is stable at room temperature for 2-4 weeks, and alpha-amylase has been shown to be stable under a range of conditions. These procedures for saliva sample collection are routinely used in the field. ENREF 98 The samples will be stored in our laboratory at -20 °C until they are delivered in a large number to be analyzed at Dresden Lab Service, a well-established biochemical assay laboratory headed by [name], in Germany, to be analyzed. Research personnel will be responsible for the transmission of saliva samples. *The saliva sampling procedures were shown to be feasible and successful* in our study involving 155 Chinese immigrant BCSs, of whom 146 (94.2%) provided at least 14 valid samples of the 16 saliva samples at baseline and 6 weeks later. Participants *did not find the procedure*, including fasting for 1 hour before sampling and mailing saliva samples, *to be burdensome*.

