**Aim 1.** Given the longitudinal nature of the study, we will use linear mixed-effects models (LMMs) to assess the effects of the interventions on outcomes. Treatment condition and time will be included and tested in the model, as well as their interaction, with adjustment for covariates including the baseline outcome value, time since diagnosis, and disease stage. If needed, we will also control for potential confounders such as demographic or other clinical variables correlated with outcome variables. Potential heterogeneity across recruitment sites will be accounted for by adding site-specific random intercepts. The repeated-measures correlation structure will be selected based on the Bayesian information criterion (BIC). The primary outcome will be a composite scale of QOL based on the FACT-B total score. Hypothesis 1.1 (QOL at 6- and 12-month follow-ups for both intervention conditions) will be tested against the control condition within the LMMs based on appropriately constructed contrasts, each with a *two-sided 0.0125 level of significance, to ensure that the overall type I error rate across the four tests does not exceed 0.05. Controlling the overall type I error rate for testing the four primary hypotheses will help increase the reproducibility of our main study findings.*

All other analyses described below will use a two-sided significance level of 0.05 without adjustment for multiple testing. The corresponding results will thus be interpreted as hypothesis-

generating. The above LMMs will be repeated for medical appointments and perceived stress as outcomes (hypotheses 1.1 and 1.2). We will conduct linear regression analyses with stress biomarkers (cortisol and alpha-amylase) as the outcomes (hypothesis 1.2). The average levels and average slope of change in the 2 days at the 6-week follow-up will be used as the outcome of interest for each stress biomarker. We will control for potential confounding variables such as medical conditions and medications.

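### The biomarker regression for hypothesis 1.2 does not name the baseline cortisol and alpha-amylase values as covariates, although the same saliva samples are taken at baseline

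*Protocol*

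**What the plan says.** Protocol section 7.0, Quantitative data analysis, Aim 1, sets out two models.

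- The linear mixed models adjust for covariates "including the baseline outcome value, time since diagnosis, and disease stage". They are then extended to two further outcomes: "The above LMMs will be repeated for medical appointments and perceived stress as outcomes (hypotheses 1.1 and 1.2"). Biomarkers are not among them.
- Biomarkers get their own model: "We will conduct linear regression analyses with stress biomarkers (cortisol and alpha-amylase) as the outcomes (hypothesis 1.2"). Its outcome is fixed at 6 weeks: "The average levels and average slope of change in the 2 days at the 6-week follow-up will be used as the outcome of interest for" both markers. On covariates the text says only: "We will control for potential confounding variables such as medical conditions and medications".

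The baseline measurements exist. Section 6.0 says "We will assess biomarkers at baseline and 6-week follow-up", and the Biomarkers entry in the same section gives one sampling schedule for both times: "Salivary cortisol and alpha-amylase levels will be assessed at study entry and at the 6-week follow-up four times a day", on each of two consecutive days. Table 1 marks saliva at baseline and 6 weeks. No sentence in the analysis section uses the baseline biomarker as a covariate, in a change score or as a repeated measure.

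**The concern.** Perceived stress and the biomarkers belong to the same hypothesis, are timed to coincide at 6 weeks, and share one power statement. Perceived stress will be adjusted for its baseline value. For the biomarkers no such adjustment is named, and no reason is given for the difference.

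Two things are lost if the regression is run as described. The part of the between-person variation that baseline would explain stays in the error term. Any chance difference between arms at study entry also carries through to the 6-week comparison in proportion to the baseline-to-follow-up correlation. Each woman gives 4 × 2 = 8 timed, fasted samples at baseline, and the stated analysis makes no use of them.

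**Working it through.** **Inputs.** From section 7.0, Power analysis: 64 evaluable per group (80 randomized, 20% attrition), standardized difference 0.499, two-sided alpha 0.05, stated power 80%. The correlation ρ between the baseline and 6-week biomarker summary is not in the protocol. It is assumed here, over 0.2 to 0.6.

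**1. Reproduce the stated figure.** Two-sample t-test, df = 2 × 64 − 2 = 126, noncentrality = d × √(n/2) = 0.499 × √32 = 2.823. Power from the noncentral t is 79.99%, and the effect detectable at exactly 80% power is 0.4991 SD. The stated figure is therefore right for an unadjusted comparison and takes no credit for baseline.

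**2. Add the baseline value.** In ANCOVA the residual SD is √(1 − ρ²) times the unadjusted SD. The detectable effect is 0.4991 × √(1 − ρ²), and the equivalent sample size factor is 1/(1 − ρ²).

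| Assumed ρ | √(1 − ρ²) | Detectable effect (SD) | Power at 0.499 SD | Equivalent extra patients |
|---|---|---|---|---|
| 0 | 1.000 | 0.499 | 80.0% | 0% |
| 0.2 | 0.980 | 0.489 | 81.6% | 4% |
| 0.3 | 0.954 | 0.476 | 83.6% | 10% |
| 0.4 | 0.917 | 0.457 | 86.4% | 19% |
| 0.5 | 0.866 | 0.432 | 89.9% | 33% |
| 0.6 | 0.800 | 0.399 | 93.8% | 56% |

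**3. Chance imbalance.** The standard error of a between-arm baseline difference is √(2/64) = 0.177 SD. With an assumed ρ of 0.5, an imbalance of two standard errors (0.354 SD) would move the 6-week estimate by 0.5 × 0.354 = 0.177 SD. That is 0.177/0.499, or about 35%, of the effect used for power. The unadjusted standard error already allows for such draws on average; adjustment removes most of their influence in the trial actually run.

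**4. ANCOVA against a change score.** A change score has SD √(2(1 − ρ)). Power at 0.499 SD would be 60.0% at ρ = 0.2, 65.8% at 0.3, 72.5% at 0.4, 80.0% at 0.5 and 87.9% at 0.6. Below ρ = 0.5 this is worse than ignoring baseline, and at every value in the table it is worse than ANCOVA. How the baseline is used therefore matters.

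**The case against.** Several points on the other side stand.

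- The protocol omits the baseline value; it does not exclude it. The list of confounders is open-ended, so it would be wrong to say that adjustment is confined to conditions and medications. An analysis plan that is not at hand could add the baseline. Still, the open list concerns confounders, whereas the baseline outcome is mainly a precision covariate that the same section names where it is wanted. The protocol has already fixed the model, the outcome and the kind of covariate, so this is more than a detail left for later.
- A reader might infer that the 6-week comparison is biased. It is not: randomization makes it unbiased without baseline adjustment.
- A reader might infer that the power statement is wrong. It reproduces, and it matches an unadjusted analysis.
- A reader might infer that hypothesis 1.2 concerns within-person change and so goes untested. Its wording is about normalizing levels at 6 weeks, which a between-arm contrast at 6 weeks addresses. ANCOVA estimates the same contrast more precisely.
- The gain could be small. The power statement is for the cortisol slope, a summary from four samples a day over two days, and nothing in the protocol supports a high correlation for it. At ρ = 0.2 the gain equals only about 4% more patients.
- The 64 per group reflects attrition at 12 months. More women may be evaluable at 6 weeks, in which case the unadjusted detectable effect is already below 0.499. The relative gain from adjustment would be the same.
- Adjustment is not entirely free, because some baseline saliva will be missing. In the team's earlier study 146 of 155 women (94.2%) gave at least 14 of 16 valid samples over both time points.

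**Conclusion.** The point holds as a missed improvement, not as an error. As written, the biomarker regression compares arms on 6-week values, and the baseline samples have no stated role. Under randomization this costs precision and leaves the estimate open to chance baseline imbalance. For assumed correlations of 0.2, 0.3, 0.4, 0.5 and 0.6, naming the baseline value would lower the detectable effect with 64 per group from 0.499 to 0.489, 0.476, 0.457, 0.432 and 0.399 SD. The size rests wholly on that correlation, which the protocol does not give.

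The weight is modest. These tests use an unadjusted 0.05 level and are declared hypothesis-generating, and the primary quality-of-life analysis is unaffected. A pre-specified choice also removes the option of picking between adjusted and unadjusted biomarker results after seeing the data.

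**What to change.** In section 7.0, Aim 1, state that for each biomarker and each summary (mean level and diurnal slope) the 6-week value will be regressed on arm, the same summary at baseline, the three minimization factors (time since diagnosis, disease stage, age of migration) and the stated medical-condition and medication covariates. Specify ANCOVA and not a change score.

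Add that women with 6-week but no usable baseline saliva stay in the analysis, for example by imputing the baseline covariate.

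The change costs a sentence or two. It needs no new samples, visits or patients, and the stated sample size can stay as it is. The one added task is handling missing baseline saliva.

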## 7.0 Data and Specimen Banking

**Power analysis.** Power analysis is based on testing hypotheses 1.1 in Aim 1 (primary aim) for the primary endpoints (QOL evaluated at 6 and 12 months) using nQuery 7.0. A sample size of 64 in each group (80 original, 20% attrition at 12 months, an assumption based on preliminary study 2) will have at least 80% power to detect a difference in mean QOL of 0.60 standard deviation (SD) using a two-sample *t*-test with a two-sided **0.0125 significance level (with a Bonferroni adjustment for the four primary comparisons)**. The *t*-test is appropriate to estimate power because the primary hypothesis is specified as contrasts at specific time points. The effect size of 0.60 was estimated from preliminary study 2, which compared expressive writing with the control at 6 months. For the same reason, we expect that the self-cultivation intervention condition will have an effect size of 0.6 at the follow-ups. The same sample size will have 80% power to detect a standardized effect size of 0.499 (a medium effect size) in between-group differences in cortisol slopes and perceived stress (hypothesis 1.2), to detect a standardized effect size of 0.251 of the interaction between acculturation and treatment conditions (hypothesis 2.1), and to detect a mediation effect (standardized coefficient of 0.35 in the *b* path and standardized between-group difference of 0.60) (hypothesis 3.1), with a 0.05 two-sided significance level.

**Quantitative data analysis.** Before we begin inferential procedures, we will conduct extensive descriptive analyses on the data collected. Distributional assumptions will be evaluated, and if indicated, normalizing (such as log) transformations or robust procedures will be used. Appropriate procedures to assess the validity and reliability of questionnaires will be used.

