**Aim 2.** To characterize the moderation effect of acculturation/enculturation on the intervention (hypothesis 2.1), we will use LMMs like those in Aim 1 but test additional interaction effects between acculturation/enculturation subscale composite scores and intervention conditions. Items to assess the language aspects in the acculturation/enculturation subscales will also be explored as potential moderators. Furthermore, we will test interaction effects between intervention conditions and additional potential moderators (time since diagnosis, age, age of migration, , intervention delivery modes (receiving instructions via mail and writing by hand vs. receiving instructions and writing online), because the effects of the interventions may also depend on these factors. For example, those who are more recently diagnosed or more comfortable writing in Chinese may benefit more from the interventions.

**Aim 3.** To identify potential mechanisms by which the expressive writing intervention yields health benefits (hypothesis 3.1), we will conduct a longitudinal mediation analysis. Specifically, we will use measures of QOL outcomes at 6- and 12-month follow-ups and each of the potential mediators (posttraumatic growth, relationship harmony, and self-stigma) at 6-week and 6-month follow-ups, respectively, in the a and/or b paths of the mediation models (each path being a LMM). We will use bootstrapping in testing for the indirect effect of each mediator on QOL outcome. We will also explore multiple mediator models in case more than one mediator emerges.

**Missing data and dropouts.** The LMMs, as a likelihood-based regression method, will give valid (e.g., asymptotically unbiased) estimates of effects provided that the missingness probability depends only on the observed variables in the model (missing at random). However, data may not be missing at random; thus, we will conduct sensitivity analyses assuming different missing data mechanisms, especially when the attrition rate is moderate or high (e.g., >10%) and/or the attrition is unbalanced across intervention conditions. We will consider multiple imputation approaches based on relevant baseline participant characteristics to account for the missing-at-random mechanisms. We will also explore pattern-mixture and selection models to account for potential missing-not-at-random mechanisms.

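### The planned multiple imputation names only baseline characteristics, so for women lost between 6 weeks and 6 months it adds no post-randomization information to the primary model

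*Protocol*

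**What the plan says.** All of this is in the Protocol.

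- **Primary model (section 7.0, Aim 1).** The linear mixed model contains condition, time, their interaction, site random intercepts and covariates "including the baseline outcome value, time since diagnosis, and disease stage". Others are optional: "If needed, we will also control for potential confounders such as demographic or other clinical variables correlated with outcome variables". The primary contrasts are at two times: "Hypothesis 1.1 (QOL at 6- and 12-month follow-ups for both intervention conditions) will be tested against the control condition".
- **Missing data (section 7.0, Missing data and dropouts).** The mixed model is said to be valid "provided that the missingness probability depends only on the observed variables in the model (missing at random"). The protocol grants that this may fail and promises sensitivity analyses, especially if attrition exceeds 10% or is unbalanced by arm. For missing at random it says: "We will consider multiple imputation approaches based on relevant baseline participant characteristics to account for the missing-at-random mechanisms". For missing not at random, pattern-mixture and selection models are to be explored.
- **Expected loss (section 7.0, Power analysis).** "20% attrition at 12 months", which already exceeds the 10% mark.
- **Schedule (section 6.0, Table 1 and the text after it).** FACT-B is collected at baseline, 6 months and 12 months. Much else is collected at 6 weeks: "Potential psychosocial mediators will be self-reported at baseline and at the 6-week and 6-month follow-ups", and "We will also assess self-reported perceived stress at the 6-week follow-up". Table 1 also lists fear of recurrence, spirituality, sleep, fatigue and saliva biomarkers at 6 weeks.

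**The concern.** A missing-at-random imputation is useful beside a mixed model when it brings in information that the mixed model lacks. The best candidates here are measured after the writing sessions and before the first primary time point. The protocol's own theory (hypothesis 3.1) says that posttraumatic growth, relationship harmony and self-stigma carry the effect on QOL, and all three are recorded at 6 weeks. The imputation sentence points to baseline instead.

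At stake is whether this check can reveal a problem. If women leave after 6 weeks because of how they feel then, and this differs between arms, the mixed model is biased. An imputation from baseline data would be biased in nearly the same way. The two results would agree, and the agreement would be read as robustness.

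**Working it through.** **1. The plan's own figures.** With 64 evaluable per arm, a difference of 0.60 SD and two-sided alpha 0.05/4 = 0.0125, the noncentral t distribution has 2×64 − 2 = 126 degrees of freedom and noncentrality 0.60 × √(64/2) = 3.39. Power is 0.804, and 64 is the smallest n per arm that reaches 80%. Then 64/(1 − 0.20) = 80 per arm, or 240 in total. The stated figures reproduce, and nothing below changes them.

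**2. Which analysis uses what, by time of loss.**

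| Lost | QOL mixed model uses | Imputation as described uses | Collected, but named in neither |
|---|---|---|---|
| Before 6 weeks | Arm, site, baseline covariates | Baseline characteristics | No 6-week measures exist |
| Between 6 weeks and 6 months | The same | Baseline characteristics | 6-week stress, symptoms, biomarkers, mediators; writing sessions completed |
| Month 12 only | The same, plus 6-month QOL | Baseline characteristics; 6-month QOL not named | 6-week data; 6-month stress and mediators |

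In the second row neither analysis uses anything observed after randomization. In the third row the imputation would use less than the mixed model unless 6-month QOL is added.

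**3. Size, by illustration.** Except for the 0.60 SD effect and the 20% loss, the inputs are assumptions and not from the documents. Placing all the loss between 6 weeks and 6 months is also an assumption. There were 400,000 simulated women per arm. For each woman:

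- y0 is baseline QOL, a is another baseline variable outside the mixed model, and e is new information arising by 6 weeks. All are standard normal.
- 6-week status: w = 0.5·y0 + 0.3·a + √0.66·e + 0.4·arm (higher is better).
- 6-month QOL: y = 0.6·y0 + 0.2·a + r·e + noise + 0.60·arm, with SD 1 within arm and r = 0.2 or 0.4.
- Loss is 20% in each arm, and its log-odds fall by g per unit of w (approximately its SD), with g = 0.5, 1.0 or 1.5.

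Missing y was predicted by regression within arm. Bias is the estimated effect minus 0.60.

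Dependence in the intervention arm only:

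| r | g | y0 only (like the mixed model) | y0 and a (richer baseline) | y0, a and w (6-week added) |
|---|---|---|---|---|
| 0.2 | 0.5 | 0.022 | 0.016 | 0.000 |
| 0.2 | 1.0 | 0.043 | 0.033 | 0.004 |
| 0.2 | 1.5 | 0.055 | 0.042 | 0.002 |
| 0.4 | 0.5 | 0.039 | 0.033 | 0.001 |
| 0.4 | 1.0 | 0.069 | 0.059 | 0.000 |
| 0.4 | 1.5 | 0.090 | 0.077 | −0.001 |

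With the same g in both arms, every bias is within 0.004 of zero. The direction is not fixed. In a separate run (17% lost, stress coefficient −0.5 on QOL, log-odds slopes on stress of 0.7 in control and −0.3 in intervention), conditioning on baseline gave 0.52 instead of 0.60. Adding 6-week stress within arm restored 0.60.

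**4. Scale.** Relative to the assumed effect, 0.022/0.60 = 4% and 0.090/0.60 = 15%. The unadjusted standard error of one comparison is √(2/64) = 0.177 SD, so the bias is 0.022/0.177 = 0.12 to 0.090/0.177 = 0.51 standard errors.

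**The case against.** **Two stronger readings are tempting, and the text supports neither.** A reader might infer that the imputation conditions on no more than the mixed model does. That does not follow. The mixed model fixes three covariates, while the imputation draws on an open list of relevant baseline characteristics that could include acculturation, education, income or baseline fatigue. In the illustration a richer baseline set did lower the bias, though only from 0.022–0.090 to 0.016–0.077. A reader might also infer that post-baseline data are excluded. The sentence excludes nothing and is tentative; it simply names baseline and nothing else.

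**It is analysis-plan detail.** Predictor lists are often left to the SAP, which is not at hand. This stands in part. The protocol is not silent, however: it states a basis for the imputation, and that basis is the weaker one for this schedule.

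**It is one check among several.** Pattern-mixture and selection models are also foreseen, and dropout driven by 6-week stress is a departure that they address. That is fair. But they rest on untestable assumptions and are only to be explored, whereas the 6-week data are observed and can be used directly.

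**The size is assumed.** This stands. The documents give no dropout slopes, no timing of loss and no evidence that dropout relates to distress differently by arm. The reported response above 90% among women who completed the writing (section 6.0) suggests that much loss may come early, where 6-week data cannot help. Because the illustration puts all 20% in the 6-week to 6-month window, a smaller share there would give less bias.

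**A large imputation model would be unstable.** This also stands. Baseline QOL (1), minimization factors (2 + 3 + 1 = 6), 6-week stress (1), all nine mediators (9), sessions completed (1) and the other QOL score (1) make 19 terms, to be fitted to about 64 complete cases if done separately by arm. The simulation had 400,000 per arm and one auxiliary variable, so it does not show that such a model would work here.

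**Conclusion.** The point holds as a weakness in a sensitivity analysis. The imputation is described from baseline characteristics with no post-baseline variable named. For women lost between 6 weeks and 6 months it therefore adds no post-randomization information to the mixed model, and for those missing only month 12 it could use less. If dropout depends on 6-week status differently by arm, the shared bias is about 0.02 to 0.09 SD under the assumed inputs, and 6-week data reduce it to 0.004 SD or less. If the dependence is equal across arms, there is about none. The conclusion assumes that a material part of the 20% is lost after the 6-week visit. The primary analysis, sample size, power and alpha are not affected.

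**What to change.** Replace the sentence on multiple imputation with one stating that the imputation model includes:

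- treatment condition, either by imputing within arm or by adding arm interactions for the key auxiliary variables;
- baseline QOL and the three minimization factors (time since diagnosis, stage, age of migration);
- 6-week perceived stress and a small prespecified set of 6-week mediators, for example the three in hypothesis 3.1;
- number of writing sessions completed;
- all observed 6- and 12-month QOL.

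Analyse the imputed data with the primary mixed model.

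Keep the set small for about 80 women per arm. With three mediators the count is 1 + 6 + 1 + 3 + 1 + 1 = 13 terms instead of 19. If that is still too many within arm, a joint model with arm interactions for only the key auxiliaries is lighter.

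The variables are already collected, so the cost is one sentence and modest programming. It should be fixed before outcome data are seen.
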